#### Dropout rates

Dropout rates will be compared at the end of the study with the non-parametric criterion Mann Whitney (IV: group assignment and DV: number of drop outs), as number of drop-outs is an ordinal variable.

The Statistical Package for the Social Sciences (SPSS) version 25 (95) will be used for the statistical analyses. All significance tests will be two-tailed, with a 5% significance level and 95% confidence interval.

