**Method and design:**

A quasi-experimental clinical trial will be conducted. The study is designed to include 212 BPD patients who will be non-randomly assigned to specialized health care services and to two TAU centers. Patients will be recruited at each site following the routine clinical pathways of referral at each center. The primary outcome measures are BPD severity, suicide attempts and hospital admissions. The secondary outcome measures will include measures of general psychopathology, psychosocial functioning, quality of life and retention in treatment. In addition. An economic evaluation from a societal perspective will be conducted.

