**Figure 1 f1:**
[figure not shown]
Flowchart of the study design.

Primary outcomes will be (i) the severity of BPD symptoms and (ii) the severity of self-harm and suicidality. Secondary outcomes will be: (i) psychopathological symptom severity, (ii) quality of life, (iii) quality and intensity of interpersonal relations, (iv) functioning and (v) disability.

Mediator variables will be: (i) reflective functioning, (ii) defense style and (iii) personality organization. In other words, better primary and secondary outcomes for the intervention group as opposed to TAU group are expected to be discerned due to differences in reflective functioning, defense style and personality organization. As the design does not include random allocation of participants in the two arms, baseline measurements of the outcome variables will be considered as confounders for the ensuing measurements. Moreover, the two groups will be compared in terms of the following variables: sex, family status, education status, number of children, profession, living arrangement, physical illness, medication for BPD and prior hospitalize physical illness, medication for BPD and prior hospitalization. Those variables with a statistically significant difference between the two groups, will be considered confounder variables in the design and will be taken into consideration as such in ensuing evaluation points. Moreover, information about the treatment delivered in the two groups will be recorded; namely, duration of treatment, type and number of sessions attended. These will be included as confounder variables in the design.

The Ethics Committees of Eginition Hospital, Medical School of the National and Kapodistrian University of Athens (No. 404/05-07-2021), Attikon Hospital (No. 443 25/08/2021), and Sismanogleion General Hospital (27703/10-12-2021) approved the research protocol. The Clinical Trials.gov website has registered the trial under the ID NCT06392139 (Protocol ID No. 404/06-07-202).

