### Primary outcome measures

The primary outcome measures include the severity of BPD and severe parasuicidal behavior. 331 The BPDSI (Borderline Personality Disorder Severity Index-Leibniz Institute for Psychology) (64) is a semi structured clinical interview measure that captures specific BPS symptoms over the past three months. It contains 70 items, which are similar to the DSM-IV criteria. It covers nine areas of symptoms: *(1) abandonment; (2) interpersonal relationships; (3) identity; (4) impulsivity; (5) parasuicidal behavior; (6) affective instability; (7) emptiness; (8) outbursts of anger; and (9) dissociation and paranoid thoughts* (64). For its reliability, the internal consistency is greater than alpha = .90 (total score) or between alpha = .49 and.89 (subscales) (65). It is a reliable and valid instrument that is suitable for use as an outcome measure (64, 66). In our sector’s validation procedure of the BPDsi (67, 68), the statistical analyses revealed a fairly valid and reliable tool (Cronbach’s α = .99). A cutoff score of 15 between patients and controls has been established; thus, a score below 15, which is rated two years after randomization or earlier and maintained until follow-up, is used as a criterion for recovery (64).

**Suicide and Self-Harm Inventory** (69): The purpose of the interview is to collect accurate data about attempted suicides and self-harm incidents over a six-month period without attempting to measure their severity. Bateman and Fonagy (70, 71) define parasuicidal behavior as including three types of behavior: *1) suicide attempts (which must be intentional, life-threatening, and require medical intervention); 2) life-threatening self-harm behaviors (which must be intentional, cause visible tissue damage, and require nursing or medical intervention); and 3) admissions to a psychiatric hospital*. The Greek version will be used here (72).

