#### Evaluation of effect

For evaluating the effect of the group assignment (intervention *vs* control) on the primary and secondary outcome variables, multiple linear regression models will be computed for each outcome variables. As predictors the following variables will be inserted: the baseline measurement of the outcome variable of interest, treatment duration, number of sessions attended and all variables that emerged as confounders at baseline (i.e. socio-demographic and other variables that were significantly different across groups).

This analysis will be replicated for all evaluation time points: T_1_ – T_4_. For time points T_6_-T_10_, it will occur only for the two primary outcome variables.

At the end of the study, a Repeated Measures ANOVA with the group assignment (IV) and the 11 time points of assessment (baseline, T_1_ – T_10_) will be performed for the two primary outcome variables.

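### The primary outcomes are worded inconsistently and tested at 5% at every analysed visit, with no primary visit, primary analysis or rule for two outcomes, so no single result decides the main hypothesis

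*Protocol article*

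**What the plan says.** **Primary outcomes.** The abstract (Method and design) has three: "The primary outcome measures are BPD severity, suicide attempts and hospital admissions". The Design section has two: "Primary outcomes will be (i) the severity of BPD symptoms and (ii) the severity of self-harm and suicidality". The Primary outcome measures section has "The primary outcome measures include the severity of BPD and severe parasuicidal behavior", and defines the second item as suicide attempts, life-threatening self-harm and psychiatric admissions together. The inventory that supplies this second outcome is there to "collect accurate data about attempted suicides and self-harm incidents over a six-month period without attempting to measure their severity".

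**Tests.** Evaluation of effect plans one multiple linear regression per outcome and visit: "This analysis will be replicated for all evaluation time points: T_1_ – T_4". It continues: "For time points T_6_-T_10_, it will occur only for the two primary outcome variables". T5 is an assessment visit in Table 1 but is not in this list. A repeated measures ANOVA over 11 time points follows at the end of the study, for the same two outcomes. The level for every test is given under Dropout rates: "All significance tests will be two-tailed, with a 5% significance level and 95% confidence interval".

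**What is tested for.** Aims and hypotheses sets the primary aim over a 2-year follow-up with four post-enrolment time points and singles out none of them. Sample size gives 106 per group for power 0.90 at Cohen's d = 0.45.

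**The concern.** Two gaps compound each other. First, a reader cannot tell whether hospital admissions are a primary outcome in their own right (abstract), part of a composite (Primary outcome measures), or not primary at all (Design). Nor can the reader tell how severity of self-harm would be obtained from an instrument that does not attempt to measure it. Second, whichever definition is used, each primary outcome is tested at nine visits and once more in the ANOVA, each time at 5%, and nothing says which result settles the clinical part of hypothesis 1.

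The 5% level therefore holds for each test but not for the trial's claim. A significant difference in one outcome at one visit could be reported as the primary success. This is not a detail left to an unseen analysis plan: the article itself fixes both the list of repeated tests and the level for each.

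**Working it through.** **1. The plan's own figure.** Inputs: d = 0.45, power 0.90 and 1:1 allocation (Sample size); two-sided 5% (Dropout rates).

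n per group = 2(z₀.₉₇₅ + z₀.₉₀)²/d² = 2(1.960 + 1.282)²/0.45² = 103.8, so 104. The exact t-test gives 104.7, so 105. The stated 106 has power 0.903. The figure reproduces, and it is the size for one two-group comparison at 5%.

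**2. Number of primary tests.**
- 2-year primary aim: 2 outcomes × 4 visits (T1–T4) = 8.
- All listed visits: 2 outcomes × 9 visits (T1–T4 and T6–T10) = 18.
- The two repeated measures ANOVAs come on top and are left out of the counts below.

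Two outcomes are used because Evaluation of effect refers to two primary outcome variables.

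**3. Upper reference: independent tests.** P(at least one false positive) = 1 − 0.95^k.
- k = 8: 1 − 0.95⁸ = 0.337.
- k = 18: 1 − 0.95¹⁸ = 0.603.

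**4. Correlated tests.** The documents give no correlation between visits or between outcomes, so these are assumptions: equal correlation between visits from 0.3 to 0.9, and 0.4 between outcomes. The test statistics were simulated as multivariate normal under no effect (400,000 draws), counting any |z| > 1.96. The one-direction column counts only false results in favour of the service.

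| Visit correlation | 8 tests, either direction | 8 tests, favouring service | 18 tests, either direction | 18 tests, favouring service |
|---|---|---|---|---|
| 0.3 | 31% | 16% | 53% | 28% |
| 0.5 | 28% | 14% | 45% | 23% |
| 0.7 | 23% | 12% | 35% | 18% |
| 0.9 | 17% | 9% | 22% | 11% |

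The reference levels for one test are 5% in either direction and 2.5% in one direction. Every cell is well above its reference.

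**5. Price of controlling the error at N = 212** (normal approximation, 106 per group, d = 0.45).
- One confirmatory test at 5%: power 0.91.
- 0.025 for each of two outcomes at one visit: power 0.85.
- Bonferroni over 18 tests (0.05/18 = 0.0028): power 0.61.

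Naming one test and ordering the second after it keeps the planned power for the first. Correcting across all visits does not.

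**The case against.** **The size is assumed, not given.** This stands. No correlations are stated, so an error rate such as 35–45% cannot be read as a property of the plan. It is the part of the 18-test range that goes with visit correlations of about 0.5 to 0.7.

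**The relevant family is 8 tests, not 18.** This largely stands. The primary aim is a 2-year one, and the later visits are presented as a longer-term evaluation. The 8-test figures are therefore the ones to weigh against hypothesis 1.

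**No rule says that one visit suffices, and a repeated measures ANOVA covers all time points.** This is true, but the ANOVA is not named as primary and no rule excludes an isolated visit. The error rates are conditional on that reading and are labelled so.

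**Errors in favour of TAU would not support the hypothesis.** Correct. Roughly half of each correlated figure favours the service, and that half is still several times 2.5%.

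**The definitions overlap.** They do. The abstract's suicide attempts and admissions are two of the three components of the parasuicidal construct, and the body of the article consistently has two domains. A reader might infer three primary outcomes and 27 regressions from the abstract, but Evaluation of effect speaks of two primary outcome variables, so that count is not supported. The conflict over admissions, and over severity versus incidents, remains.

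**T1.** Phase 1 lasts 6–8 months and T1 is at 6 months, so a reader might infer that a T1 comparison does not test the service at all. The section on the STP-BPD does not support this: it describes the reception clinic as the first phase of the intervention, with its own monthly sessions. T1 is a legitimate comparison of an early part of the service.

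**Conclusion.** The point holds. The article states its primary outcomes inconsistently, tests two of them repeatedly at an unadjusted 5%, and does not say which result decides hypothesis 1, while its sample size is that of a single comparison.

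If any significant visit may count, the chance of at least one false positive is about 17–31% on the 2-year aim (34% if independent) and about 22–53% over all 18 tests (60% if independent). These ranges rest on assumed visit correlations of 0.9 down to 0.3, an assumed outcome correlation of 0.4, and a success rule that the article leaves open. The exact size is uncertain. That it exceeds 5% is not: it did so under every correlation tried.

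The matter should be settled before outcome data are analysed. The Limitations section says that consultation with a statistician is still to come, so there is a natural occasion for it.

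**What to change.** 1. Use one primary outcome definition in the abstract, Aims and hypotheses, Design, Primary outcome measures and Evaluation of effect. State where hospital admissions belong. Describe the second outcome as incidents, not severity.
2. Name one confirmatory test at two-sided 5%. BPDSI total at T4 (24 months, the end of the main follow-up) is one option. A single prespecified longitudinal model over T1 to T4 is equally acceptable.
3. Test parasuicidal events second in fixed sequence, only if the first test is significant. Count only events reported at T1 to T4 and adjust for the baseline count. Events reported at T0 precede allocation and must not enter the outcome.
4. Report all other visits, including T5 to T10, as supportive, with confidence intervals and no primary claim.

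The cost is wording only. The sample size need not change, because the first test keeps its full 5%. The price is that an isolated significant result at another visit can no longer be called primary, and that the parasuicidal outcome cannot be claimed if the first test fails.

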## Evaluation of cost effectiveness

### Cost measurement

#### Cost interview

An interview will be conducted to retrospectively assess the cost of illness over the past six months. These costs will include direct expenses—such as healthcare-related costs (e.g., hospital visits, psychiatric and psychological consultations, medication use, hospitalizations)—and indirect expenses, encompassing both patient and family burdens (e.g., informal caregiving by relatives or friends, out-of-pocket expenses for substances like alcohol, drugs, and tobacco) as well as broader societal costs, such as productivity loss. The recall period for the interview is 6 months (62).

### Utility measures

A five-item self-report measure (EuroQol-5D-3 L) (96, 97) will be used to assess five different dimensions of patients’ health-related quality of life: self-care, mobility, usual activity, anxiety/depression, and pain/discomfort. Quality adjusted life years (QALYs) based on EuroQol-5D-3 L data will be calculated to compare the quality of life of the participants in the intervention and the TAU programs. The EuroQol-5D-3 L scores range between 0 and 100 to provide a single index measure of the health status of patients.

### Analyses

The economic evaluation will include both a cost-effectiveness analysis (CEA) and a cost-utility analysis (CUA) based on the intention-to-treat principle. The cost interview data will be screened for irrational responses and outliers in patients’ estimates, which will be investigated on a case-by-case basis and, if necessary, dealt with by establishing decision rules. Intermittent missing values are not imputed. The amounts of resource use measured in the cost interview will be multiplied by their corresponding unit costs and then summed to arrive at a total cost. The unit costs will be based on Greece’s average unit prices. As the study covers three years, the unit costs alternate according to the average prices of each year. We also consider productivity losses, informal care, and voluntary work. Using multilevel modeling techniques, the cost-effectiveness and cost–utility ratios will be analyzed.

## Qualitative study on patients’ perspectives

Patient viewpoints are crucial in shaping public policy and offer valuable insights for the enhancement of mental health services (35, 98). Patients randomly selected from the specialized therapy program and from the treatment, as usual, (TAU) centers will be invited to participate in interviews aimed at gathering information regarding their perspectives and experiences with the service and therapy provided. It is projected that interviewing 12 patients in each group will suffice to achieve thematic saturation (99).

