2. *The second phase of the program consists of* sp*ecific interventions*. Clinical criteria (‘readiness for therapy’, self-harm, suicidality, emergency room visits, need for hospitalization, etc.) and availability (e.g., twice a year in therapy groups, once a year in the day hospital, while a small number of patients enroll each year in individual psychoanalytic psychotherapy) determine the assignment of patients to one (or more) of these interventions. The following specific interventions are available:

*Group psychoanalytic psychotherapy*: This is the main intervention, with a capacity of approximately 50 patients, in groups of 8–10 patients. It lasts for 3 years and offers one or two 90-minute sessions per week.
*Individual psychoanalytic psychotherapy*: capacity of 4–8 patients. It lasts for 2 years and offers one 45-minute session per week.
*Group or individual psychodynamic art therapy*: capacity of 4–12 patients. Last 2 years and offers one two-hour group session or one 60-minute individual session.
*Day hospital program*: The day hospital program can accommodate up to 9 patients. It includes a combination of group and individual psychotherapeutic interventions (psychoanalytic psychotherapy, art therapy, drama therapy) and psychiatric management. The day hospital program lasts 9 months. After their completion, the participants continued in group psychoanalytic psychotherapy for an additional 3 years.
*Parent groups or parent couples’ professional counseling*: parents of all-day hospital patients and a limited number of outpatients can participate in parent groups or parent couples’ psychoanalytic counseling. It lasts for one year and provides one 90-minute group or couples session per week.
*Psychiatric management and pharmacotherapy*, if required (1 session per month). Supervision is offered fortnightly for all psychotherapy interventions and weekly for psychiatric interventions.

During phase 2, in case of crisis, the patient contacts his/her psychotherapist or psychiatrist by telephone and, if necessary, goes to the emergency room of Eginition Hospital. In cases of hospitalization, the patient continues the program after discharge.

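### Twelve STP-BPD interviewees chosen at random, with no stratification stated, may leave out one of the three small therapy tracks, so the saturation projection may not extend to the whole service

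*Protocol article*

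**What the plan says.** The section Qualitative study on patients' perspectives sets the selection method: "Patients randomly selected from the specialized therapy program", and likewise from the TAU centres, are to be invited to interview. The interviews are to cover patients' views and experience of both the service and the therapy. On size, the section projects that "interviewing 12 patients in each group will suffice to achieve thematic saturation", with a citation and no calculation. It names no strata, quotas or purposive rule. It does not say whether the STP-BPD frame is the whole programme or only its second phase, or when the interviews take place.

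The section The STP-BPD, under Treatments, describes what is being sampled. Phase 1 is a reception outpatient clinic with 50 places. Phase 2 has four therapy tracks for patients:

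- Group psychoanalytic psychotherapy: "This is the main intervention, with a capacity of approximately 50 patients, in groups of 8–10 patients".
- Individual psychoanalytic psychotherapy: "capacity of 4–8 patients. It lasts for 2 years".
- Group or individual art therapy: "capacity of 4–12 patients. Last 2 years".
- Day hospital: "The day hospital program can accommodate up to 9 patients".

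The same section says that a patient may be assigned to more than one of these, and that day-hospital patients move on to group psychotherapy for three further years. TAU is delivered in two outpatient clinics.

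**The concern.** The tracks differ in format, intensity and duration, and the Discussion presents this variety of options as a central feature of the model. A sub-study meant to inform how the service is shaped should therefore hear from patients in each option. With 12 interviews and one track far larger than the others, an unstratified random draw returns mainly group-therapy patients, plus reception-phase patients if they are in the frame. It can easily contain nobody from a track with four to twelve places.

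At this size, random selection gives almost no inferential precision to set against the lost coverage. Its real benefit is protection against hand-picking, and drawing at random within strata keeps that. At stake is whether themes reported as saturated can be read as describing the whole STP-BPD or only its larger parts. No primary, secondary or economic outcome depends on this.

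**Working it through.** The figure of 12 per group is a projection without a formula, so it cannot be reproduced. What can be checked is how often 12 random interviewees cover the three small tracks.

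**Inputs.** Twelve drawn (Qualitative study section). Capacities (The STP-BPD section): reception 50, group 50, individual 4–8, art 4–12, day hospital 9 when full. The mid scenario takes 6 and 8 for individual and art. Assumptions: patients are available in proportion to capacity, and 12 are drawn without replacement from N.

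**Formula.** The probability that a track, or set of tracks, holding m patients has no interviewee is

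q(m) = C(N − m, 12) / C(N, 12).

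For three separate tracks of sizes a, b and c, by inclusion–exclusion,

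P(at least one missed) = q(a) + q(b) + q(c) − q(a+b) − q(a+c) − q(b+c) + q(a+b+c).

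**Worked case: phase 2 only, lowest capacities.** N = 50 + 4 + 4 + 9 = 67.

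- Singles: q(4) = 0.4450 (individual), q(4) = 0.4450 (art), q(9) = 0.1487 (day hospital); sum 1.0387.
- Pairs: q(8) = 0.1867, q(13) = 0.0572 twice; sum 0.3011.
- Triple: q(17) = 0.0202.
- P = 1.0387 − 0.3011 + 0.0202 = 0.758.

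**Worked case: phase 2 only, highest capacities.** N = 50 + 8 + 12 + 9 = 79.

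- Singles: 0.2500 + 0.1171 + 0.2078 = 0.5749.
- Pairs: 0.0219 + 0.0422 + 0.0174 = 0.0815.
- Triple: 0.0024.
- P = 0.5749 − 0.0815 + 0.0024 = 0.496.

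**Overlap case.** Suppose individual and art patients all sit inside the group and day-hospital pool (N = 50 + 9 = 59, or 109 with reception), and day-hospital experience counts as covered by graduates now in group therapy. Then only two tracks can be missed: P = q(a) + q(b) − q(a+b). At the highest capacities in phase 2, this is 0.1418 + 0.0467 − 0.0035 = 0.185. At the lowest capacities with reception, it is 0.6228 + 0.6228 − 0.3804 = 0.865.

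**All scenarios: probability that at least one small track has no interviewee**

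| Individual / art / day hospital | Separate, phase 2 only | Separate, with reception | Overlapping, phase 2 only | Overlapping, with reception |
|---|---|---|---|---|
| 4 / 4 / 9 | 0.76 | 0.93 | 0.64 | 0.87 |
| 6 / 8 / 9 | 0.59 | 0.85 | 0.35 | 0.69 |
| 8 / 12 / 9 | 0.50 | 0.79 | 0.19 | 0.53 |

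The table takes the day hospital as full. With 5 patients there and the lowest capacities elsewhere, the separate-track figures become 0.80 (phase 2 only) and 0.95 (with reception).

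**Interviews needed without strata.** With separate tracks, a 90% chance of covering all three small tracks takes about 24–35 interviews in phase 2 only, or 39–61 with reception included. Stratification achieves coverage within 12.

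**The case against.** The strongest reply has four parts.

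1. **The method may already be stratified.** A reader might infer that the plan prescribes simple random sampling. It does not say so. Random selection within strata also fits the wording, and a condensed article may leave strata to a fuller protocol. This stands as a limit on the claim. What remains is that the article fixes a method, a number and a saturation projection which, read as written, suit this service poorly.

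2. **Tracks overlap.** Patients can be in more than one track, day-hospital patients later join group therapy, and the day hospital itself includes art therapy and individual work. This stands and matters. In phase 2 alone it brings the chance of a miss down to 0.64, 0.35 and 0.19 at low, mid and high capacities. A reader might infer that a track will probably be missed. For a phase-2 frame that is not supported in general: two of those three figures are below one half, and even separate tracks at the highest capacities give 0.496. If the frame is the whole programme, every scenario run is above one half (0.53–0.93), but the article does not state the frame explicitly.

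3. **Capacities are not enrolment.** They are places at one time. Trial patients by track and the timing of the interviews are not given. This stands, so the figures are assumption-based ranges.

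4. **No promise of coverage by track.** A reader might infer that saturation will fail for the service. The documents do not support that. The section does not claim saturation within each track, and missing a small track does not by itself refute saturation of service-level themes. The risk is only that the statement is read more widely than the sample allows.

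**Conclusion.** The point holds as a modest design improvement. The article states random selection of 12 per group without stratification by track or phase, for a programme of very unequal parts. If the draw is unstratified and availability follows the stated capacities, the chance of having no interviewee from at least one of individual therapy, art therapy or day hospital is about 50–93% with separate tracks. It is about 19–87% if tracks overlap and day-hospital graduates count as coverage. Where the true value lies depends on the sampling frame, the overlap and the actual numbers per track, none of which the article gives. The saturation statement may therefore not extend to the whole service; the documents do not show that it will fail. The consequence is confined to the qualitative sub-study.

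**What to change.** Keep 12 interviews per group and keep random selection, but draw within strata. In the STP-BPD, take at least one interviewee from each of individual therapy, art therapy and day hospital, and the rest from group therapy and the reception phase. In TAU, split the 12 between the two clinics. If strata are not used, limit the saturation statement to the tracks actually represented.

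The cost is about one sentence and no extra interviews. A minimum of one uses three interviews and leaves 12 − 3 = 9 for group therapy and reception. An unstratified draw from the whole programme would be expected to give those two parts 12 × 100/129 = 9.3 to 12 × 100/117 = 10.3, so the loss is small. A minimum of two per small track would use six of the 12, which is harder to justify for the main track. The sample would no longer be proportional to patient numbers, and one interview secures a track's presence, not saturation within it.
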